#### Exclusion criteria

2.3.2

Participants will be excluded if any of the following criteria apply:
Use of probiotics or prebiotics within 3 months prior to enrollment.Antibiotic usage within 1 month prior to enrollment.Presence of fever (axillary temperature ≥37.5 °C).Dependency on tube feeding.Severe GI conditions requiring immediate intervention (e.g., life-threatening intestinal obstruction, perforation, hemorrhage, ulcerative colitis, Crohn's disease, celiac disease, or eosinophilic esophagitis).Diagnosis of severe malnutrition, underweight status (BMI-for-age <3rd percentile), or severe immunodeficiency disorders.History of severe allergic reactions (e.g., anaphylaxis).Monogenic disorders (e.g., Fragile X syndrome, Rett syndrome).Comorbid psychiatric diagnoses, including depression, developmental speech/language disorders, intellectual disability, attention-deficit/hyperactivity disorder (ADHD), selective mutism, reactive attachment disorder, or childhood schizophrenia.

#### Withdrawal criteria

2.3.3

Participants will be withdrawn from the study if:
The participant or legal guardian withdraws informed consent due to unwillingness or inability to continue the trial.The participant fails to complete scheduled follow-up assessments.Clinical deterioration renders continued participation unsafe or impractical.Intolerable adverse reactions occur, and the investigator deems the risks of continued participation to outweigh potential benefits.Note: Participants may withdraw from the trial at any time without justification. Investigators will document the reasons for withdrawal (if provided) in the case report form and complete all feasible assessments. Participants experiencing adverse reactions will receive appropriate medical management based on their condition.

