##### FMT infusion and schedule

2.4.4.3

Once the NJ tube is confirmed to be in the correct position, patients will be positioned supine. The thawed fecal suspension (dose: 5 mL/kg) will be infused through the tube, followed by a 20 mL saline flush to clear the tube. After the infusion, patients will remain in a supine position for at least 30 min and will be required to fast for 2 h. This procedure will be repeated three times over a 5-day period (i.e., on Day 1, Day 3, and Day 5).

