### Outcome measures

2.5

The schedule for all assessments is detailed in Table 1.

**Table 1 T1:** Visit schedule.

Time Window	Within 1 month pre-FMT (Baseline)	FMT treatment period*	1 week post-FMT	2 weeks post-FMT	3 weeks post-FMT	4 weeks post-FMT (±3 days)	5 weeks post-FMT (±3 days)	6 weeks post-FMT (±3 days)***	3 months post-FMT (±3 days)	6 months post-FMT (±3 days)	9 months post-FMT (±3 days)	12 months post-FMT (±3 days)***
Informed Consent	√											
General Data Collection	√	√										
Medical History Collection	√											
Vital Signs, Height, Weight	√	√	√	√	√	√	√	√	√	√	√	√
Inclusion/Exclusion Criteria	√											
Lab Tests**	√	√						√				√
Adverse Event Documentation		√	√	√	√	√	√	√	√	√	√	√
GSRS, DSR	√	√	√	√	√	√	√	√	√	√	√	√
CARS, SRS, ABC	√								√	√	√	√
Recipient Fecal Collection	√	√	√	√		√			√	√	√	√
Donor Fecal Collection	√											

* FMT treatment period: Includes 3 FMT administrations on Day 1, Day 3, and Day 5.

** Lab tests: Baseline tests include routine blood, urine, and stool tests, liver function (ALT, AST), renal function (BUN, Creatinine), coagulation profile, and ECG. Follow-up labs at 6 and 12 months will monitor long-term safety, including: (1) Immune/Inflammatory parameters (CBC with differential, hs-CRP, ESR) and (2) Metabolic parameters (Fasting Glucose, HbA1c, Fasting Lipid Profile, Liver Function Panel, Renal Function Panel).

*** Long-term safety & efficacy follow-ups will specifically monitor long-term safety, including immune, metabolic, and neurodevelopmental parameters.

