### Safety assessment

2.6

Safety monitoring will include documentation of adverse events (AEs), serious adverse events (SAEs), and abnormal laboratory parameters throughout the study, extending to the 12-month final follow-up.
1.Definitions and Grading: AEs will be defined as any untoward medical occurrence in a participant, regardless of its suspected relationship to the intervention. SAEs will be defined as any AE that results in death, is life-threatening, requires inpatient hospitalization, or results in persistent disability. All AEs will be graded for severity using the Common Terminology Criteria for Adverse Events (CTCAE v5.0, 2018).2.Causality Assessment: The Principal Investigator (PI) will assess all AEs for their potential relationship to the FMT intervention (classified as unrelated, unlikely, possible, probable, or definitely related).3.SAE Reporting: All SAEs will be reported by the study team to the PI within 24 h of awareness. The PI will then report the SAE to the Shenzhen Children's Hospital Ethics Committee (EC) within 7 days.4.Long-Term Safety Monitoring: (New section for comment 6) In addition to routine AE/SAE reporting, the extended 12-month follow-up will specifically monitor for potential long-term risks. This monitoring will include:

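### Children who react badly are withdrawn from the study, not just from the remaining infusions, so their safety follow-up to month 12 is not secured

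*Protocol article*

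**What the plan says.** Section 2.3.3 opens its list with "Participants will be withdrawn from the study if". Two of the four grounds are clinical: "Clinical deterioration renders continued participation unsafe or impractical", and "Intolerable adverse reactions occur, and the investigator deems the risks of continued participation to outweigh potential benefits". The note below the list has two protective elements. Investigators must document the reason for withdrawal where one is given and "complete all feasible assessments". It also says: "Participants experiencing adverse reactions will receive appropriate medical management based on their condition".

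Section 2.4.4.3 schedules three infusions, on Days 1, 3 and 5. Section 2.6 documents adverse events, serious adverse events and laboratory abnormalities "throughout the study, extending to the 12-month final follow-up", and looks specifically for late allergic, atopic, autoimmune, metabolic and neurodevelopmental problems. The laboratory footnote to Table 1 says "Follow-up labs at 6 and 12 months will monitor long-term safety". Safety forms part of the primary objective in section 2.1.1.

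**The concern.** Stopping treatment and leaving the study are separate decisions, and section 2.3.3 provides only for the second. A child who tolerates the first infusion badly has good reason not to receive the next. That is no reason to stop recording what happens to the child afterwards. After Day 5 there is no infusion left to stop, so withdrawal from the study can only end observation.

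The event that triggers withdrawal would still be recorded, graded and, if serious, reported. What may be lost is its late outcome and any later event in the same child. Such losses would be selective: they would occur in children who had already reacted badly, in a trial whose primary objective includes safety and whose 12-month follow-up exists to find delayed harm.

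**Working it through.** The plan gives no figure on this point, so there is none to reproduce. The check has two parts: whether any other text repairs the rule, and how much scheduled follow-up is exposed.

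**Reading the sections together**

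- Section 2.3.3: the object of withdrawal is the study. No option to discontinue treatment only is stated.
- Sections 2.4.4.2 and 2.4.4.3 (tube placement, infusion): no rule for omitting the second or third infusion while continuing follow-up.
- Section 2.6: monitoring runs to month 12 for the duration of the study. It does not say that withdrawn children are included. The data and safety monitoring board reviews cumulative data, and nothing requires withdrawn children to be followed.
- Section 2.7.1: the set of children with at least one infusion defines who is analysed. It does not oblige anyone to collect data after early stopping.

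**Counting scheduled assessments (ticks in Table 1)**

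- Adverse event row: 11 ticks, 1 of them in the treatment period. After treatment: 11 − 1 = 10, made up of 6 (weeks 1 to 6) + 4 (months 3, 6, 9, 12).
- Laboratory row after treatment: 2 ticks (6 weeks and 12 months), of which 1 falls after week 6. The footnote instead places the follow-up laboratory tests at 6 and 12 months, so 2 fall after week 6.
- CARS, SRS and ABC row after baseline: 4 ticks (months 3, 6, 9, 12), all after week 6.

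**Assessments lost per withdrawn child**

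The lower end assumes that all feasible assessments means every later visit. The upper end assumes that it means a single exit assessment at the time of withdrawal.

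| Withdrawn | Adverse event visits | Laboratory rounds | CARS/SRS/ABC |
|---|---|---|---|
| During Days 1 to 5 | 0 to 10 | 0 to 2 | 0 to 4 |
| Between week 6 and month 3 | 0 to 4 | 0 to 1 by the ticks, 0 to 2 by the footnote | 0 to 4 |

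The width of these ranges comes entirely from one undefined phrase.

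**The case against.** The strongest reply has four parts.

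1. This is a condensed article, and procedures after withdrawal are commonly left to the full protocol. That would answer a complaint about missing detail. It does not answer this one, because the article prints the rule and its consequence, and the consequence is the problem.

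2. The instruction to complete feasible assessments is an obligation and can be read as covering all later visits, in which case nothing is lost. That reading is possible, and it is why every range starts at zero. The narrow reading is equally open, because the text gives neither visit nor horizon. The 12-month aim in section 2.6 does not settle the matter, since a withdrawn child is no longer in the study. The promise of medical management concerns care, not data collection.

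3. The grounds are conditional. Deterioration must make participation unsafe or impractical, and an intolerable reaction also needs the investigator's judgement on risk and benefit. After Day 5, participation is mostly observation, so the grounds should seldom be met. This stands: the second row of the table is the less likely case, and the main exposure is the five-day treatment window.

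4. The analysis set of children with at least one infusion foresees incomplete treatment, and multiple imputation is available for missing primary endpoint data. Both are true, but neither secures safety observations on children who have left.

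It is also fair to say that no actual consequence has been demonstrated.

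**Conclusion.** The concern holds. As written, section 2.3.3 makes clinical deterioration or an intolerable reaction a reason to leave the study, offers no way to stop infusions alone, and does not secure adverse event and laboratory follow-up to month 12 for the children concerned. The worst case for one child withdrawn during treatment is the loss of 10 adverse event visits, 2 laboratory rounds and 4 behavioural assessments; the best case is no loss. These counts rest on Table 1 and on the two readings of the feasible-assessments phrase. The number of children affected and the size of any bias cannot be derived from the document. The sponsor should make the change because it costs little and protects part of the primary objective, not because harm to the results has been shown.

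**What to change.** Reword section 2.3.3 along these lines:

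- Clinical deterioration or an intolerable reaction, judged on the investigator's existing grounds, leads to discontinuation of the remaining infusions.
- Every child who has received at least one infusion continues adverse event and serious adverse event recording, and the scheduled safety laboratory tests and scales, to month 12, unless the guardian withdraws consent to follow-up.
- The investigator may omit individual procedures that are unsafe or impractical, but adverse event contact by telephone or through records continues as a minimum.

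The third item keeps the intent of the present feasibility wording and adds the missing horizon and minimum contact.

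The cost is an amendment to protocol and consent wording; the visits and laboratory tests are already scheduled. The drawback is continued contact with families who stopped early. The guardian's right to refuse and the investigator's discretion over burdensome procedures limit that.

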#### Elimination criteria

2.3.4

Participants will be eliminated from the final analysis if:
No data are recorded throughout the trial period.Serious protocol deviations occur (e.g., unapproved concomitant therapies, non-compliance with FMT procedures).Medications or interventions that could confound trial results are administered during the study.

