#### Analysis of clinical outcomes

2.7.1

Analysis of clinical data (CARS, GSRS, SRS, ABC) will be conducted using SPSS 26.0. Continuous variables will be expressed as mean ± standard deviation. For comparisons between baseline and specific follow-up points, paired *t*-tests or Wilcoxon signed-rank tests will be used, as appropriate based on data distribution. To analyze the longitudinal changes in primary and secondary outcomes over the multiple time points, linear mixed-effects models will be employed to account for intra-subject correlations.

To ensure the highest standard of statistical analysis, we have formally engaged a qualified statistician as a consultant for this study. The statistician will be involved in the final data analysis plan, execution, and interpretation of results.

The primary analysis of clinical outcomes will be conducted on the per-protocol (PP) population, defined as all participants who complete the primary endpoint assessment at 12 months. A secondary analysis will be performed on the intent-to-treat (ITT) population, which includes all enrolled participants who have received at least one Fecal Microbiota Transplantation administration. For longitudinal data (e.g., GSRS), linear mixed-effects models are inherently robust to data missing at random. For missing primary endpoint data (e.g., 12-month CARS), multiple imputation techniques will be explored and applied if necessary, under the guidance of our study statistician.

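### The elimination rule in section 2.3.4 removes treated children that both analysis sets in section 2.7.1 keep, on grounds judged after treatment that may be linked to outcome

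*Protocol article*

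**What the plan says.** Four parts of the protocol article bear on who is analysed.

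- **Section 2.3.4 (Elimination criteria)** opens with "Participants will be eliminated from the final analysis if". Besides children with no data, it lists "Serious protocol deviations occur (e.g., unapproved concomitant therapies, non-compliance with FMT procedures") and "Medications or interventions that could confound trial results are administered during the study". It names no analysis set, no list of medications, no time window and no one to adjudicate.
- **Section 2.7.1 (Analysis of clinical outcomes)** bases the primary analysis on a per-protocol set, defined solely by completing the 12-month assessment. The secondary analysis uses an ITT set that "includes all enrolled participants who have received at least one Fecal Microbiota Transplantation administration". Neither definition mentions deviations or medication.
- **Section 2.4.5 (Control of confounding variables)** has concomitant medication recorded at each visit and treated as a possible covariate in exploratory models.
- **Section 2.3.3 (Withdrawal criteria)** withdraws a child from the study on several grounds, among them "The participant fails to complete scheduled follow-up assessments" and "Clinical deterioration renders continued participation unsafe or impractical". Its note adds: "Investigators will document the reasons for withdrawal (if provided) in the case report form and complete all feasible assessments".

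**The concern.** Sections 2.3.4 and 2.7.1 cannot both be followed. If section 2.3.4 prevails, the ITT analysis is no longer an all-treated analysis, and the per-protocol set loses completers whom its own definition includes.

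The grounds for removal arise after treatment and depend on someone deciding what could confound, in a trial where everyone knows the treatment and can see the child's course. Two other sections show how this can be tied to outcome:

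- Section 2.3.1 allows no new psychotropic drug and no dose change during the study, so a child medicated for worsening behaviour has deviated from the protocol and is open to elimination.
- Section 2.5.2 counts use of GI medication towards an abnormal day in the Daily Stool Record, so an event scored as a poor outcome could also remove the child.

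With no control arm, any selection passes directly into the change from baseline, and no comparator can absorb it.

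**Working it through.** **1. The text, applied to one child.** Take a child who receives all three FMTs, starts a possibly confounding medication during follow-up, and attends the 12-month assessment.

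| Rule | Status of the child |
|---|---|
| 2.7.1, ITT | in (at least one FMT) |
| 2.7.1, per-protocol | in (12-month assessment completed) |
| 2.4.5 | in, with medication as a possible covariate |
| 2.3.4 | out of the final analysis |

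Three rules keep the child and one removes the child. A child who has been removed cannot contribute a covariate value either.

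**2. The plan's own sample size (section 2.8).** Inputs: SDs 6.5 and 6.7, r = 0.5, δ = 4.2, two-sided α = 0.05, power 80%, dropout 20%, enrolment 30.

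- σd = √(6.5² + 6.7² − 2 × 0.5 × 6.5 × 6.7) = √43.59 = 6.60
- n = (1.96 + 0.8416)² × 6.60² / 4.2² = 19.4, rounded up to 20
- 20 / (1 − 0.20) = 25

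The stated figures reproduce. The calculation allows for dropout and has no term for elimination.

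**3. Bias if removal is selective (assumed inputs).** Let f be the share of children removed and D the number of points by which they improved less than those kept. The mean over all children is the kept mean minus f × D, so analysing only those kept overstates the reduction by f × D. The documents give neither f nor D. I take f = 10–30%, with D equal to the plan's δ (4.2) or one SD of the difference (6.6).

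| f | D = 4.2 | D = 6.6 |
|---|---|---|
| 10% | 0.42 | 0.66 |
| 20% | 0.84 | 1.32 |
| 30% | 1.26 | 1.98 |

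For D = 4.2 this is 10–30% of the 4.2-point target.

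**4. False-positive risk under the same assumptions.** Suppose the true mean change over all 30 children is zero and the SD among those kept stays at 6.6. With k = 27, 24 or 21 kept, the test statistic follows a noncentral t with noncentrality (f × D / 6.6) × √k. The chance of a significant result in favour of FMT, nominally 2.5%, becomes 5.0%, 8.7% and 13.0% for D = 4.2, and 7.2%, 15.4% and 25.8% for D = 6.6.

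**5. Numbers left.** Two-sided paired t-test, δ = 4.2, SD = 6.60, fractions of a child rounded down:

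| Situation | Children | Power |
|---|---|---|
| All 30 kept | 30 | 92.0% |
| 20% dropout | 24 | 84.7% |
| plus 10% eliminated | 21 | 79.2% |
| plus 20% eliminated | 19 | 74.7% |
| plus 30% eliminated | 16 | 66.3% |

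The plan's formula is a normal approximation with a minimum of 20. By that yardstick 21 is still enough and 19 is not.

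**The case against.** **Section 2.7.1 is the specific text on analysis sets.** Read alone it removes no treated child from ITT, and a later analysis plan would normally map elimination criteria to sets. ITT is also only the secondary analysis, and the trial calls itself exploratory. This limits the consequence but does not remove the conflict: section 2.3.4 speaks of the final analysis without restriction, and its items are missing from the per-protocol definition too.

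**Section 2.4.5 might cover only medications not judged confounding.** That is possible, but the article draws no such line.

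**The direction of bias is not proven.** This stands. A medication may have nothing to do with the course of ASD, such as an antibiotic for an intercurrent infection. And in a pre-post design, keeping a child who starts an effective new therapy credits that therapy's benefit to FMT, so retention can inflate the result as well.

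**Stronger readings of the withdrawal rule.** A reader might infer that section 2.3.3 also contradicts the ITT definition, or that a single missed visit ends a child's participation. With ten follow-up visits and independent miss rates of 2%, 3% or 5%, 1 − (1 − p)¹⁰ would then affect 18%, 26% or 40% of children. The documents do not support this. Section 2.3.3 withdraws children from the study, not from the analysis; it gives no number of missed assessments; it asks for all feasible assessments to be completed; and the miss rates are invented. Those percentages carry no weight here.

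**Conclusion.** The contradiction between sections 2.3.4 and 2.7.1 is established from the text and needs no assumption. Section 2.4.5 adds a third, differing treatment of concomitant medication. Followed as written, section 2.3.4 removes treated children on judgement-based grounds that arise after treatment and can be related to outcome.

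That this would bias the CARS change towards benefit is probable, not certain, and its size cannot be known from the documents. The 0.42–1.26 points rest on an assumed removal share of 10–30% and an assumed 4.2-point gap. The loss of power rests on assumed elimination rates on top of the planned 20% dropout.

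A reader might go further and conclude that the all-treated analysis is bound to favour FMT. That would require both that section 2.3.4 overrides section 2.7.1 and that the removed children did worse; the article establishes neither. The withdrawal wording is a lesser, separate matter of clarity.

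**What to change.** 1. In section 2.3.4, state that the deviation and medication items do not apply to the ITT analysis and define a sensitivity set only. In section 2.7.1, repeat that every child with at least one FMT stays in ITT; gaps in such a child's data are a matter for the mixed model and, where used, multiple imputation.
2. Align section 2.4.5 with this, so that concomitant medication has one stated role.
3. Record the start date of any new medication or therapy, and add one sensitivity analysis that sets data after that date to missing. This addresses the opposite risk, that another treatment's effect is credited to FMT.
4. In section 2.3.3, state that missed assessments alone do not end data collection. This agrees with its own note on feasible assessments and with the planned mixed model. Nothing here touches the clinical withdrawal items (deterioration, adverse reactions).

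The cost is wording in four sections, one CRF date field and one sensitivity run. It should be settled before outcome data are examined, since exclusions chosen afterwards in an open-label single-arm trial cannot be defended.

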### Study procedures and content

2.4

#### Recruitment, screening, and management of healthy fecal donors

2.4.1

Donor selection is critical to the safety of FMT. Our protocol is designed in strict accordance with international consensus guidelines, including the European Consensus Conference on Faecal Microbiota Transplantation, the International Consensus Conference on Stool Banking, and joint NASPGHAN/ESPGHAN recommendations for pediatric FMT (34, 35).

##### Multi-step donor screening protocol

2.4.1.1

Potential donors undergo a rigorous, multi-step screening process to minimize the risk of transmitting infectious or microbiota-mediated diseases.

Step 1: Clinical Assessment and Exclusion. The initial phase involves a detailed questionnaire, a clinical interview, and a physical examination. Individuals are excluded based on:
GI Conditions: History of inflammatory bowel disease (IBD), irritable bowel syndrome (IBS), chronic constipation or diarrhea, celiac disease, or GI malignancies.Other Medical Conditions: History of autoimmune diseases, atopic conditions (asthma, eczema), metabolic syndrome, diabetes, chronic pain syndromes, or significant neurological or psychiatric conditions.Medication Use: Antibiotic use within the past three months; current use of immunosuppressants, systemic antineoplastics, or chronic proton pump inhibitors.Infection Risk Factors: Recent infectious symptoms (e.g., fever), recent travel to high-risk regions, or frequent contact with healthcare settings [to mitigate risk of multidrug-resistant organism (MDRO) colonization].Step 2: Comprehensive Laboratory Screening. Eligible candidates from Step 1 proceed to extensive laboratory testing.
Serological (Blood) Screening: Tests for HIV-1/2, Hepatitis A, B, and C, and syphilis. A complete blood count, comprehensive metabolic panel, lipid profile, hs-CRP, and fluorescent antinuclear antibody tests are also performed.Stool Screening: Samples are meticulously tested to exclude pathogens.Bacterial Pathogens: Salmonella, Shigella, Campylobacter, Yersinia, and *Clostridioides difficile* toxin.Viral Pathogens: Rotavirus, adenovirus, and norovirus.Parasites: Ova and parasites, including Giardia and Cryptosporidium.Specialized Testing: Given the upper GI administration route, donors are screened for Helicobacter pylori (stool antigen test). In line with current safety standards, stringent screening for MDROs is conducted, including for ESBL-producing Enterobacteriaceae, VRE, CRE, and MRSA.

